#### Sensitivity analysis

The 10-year period of data collection represents a long time period over which clinical practice and outcomes may have changed. To assess for this, we will estimate the yearly prevalence of clinical deterioration and note any statistically significant changes in outcome over time. In addition, because NICE guidelines were updated in 2014 (with minor changes to the indications for CT brain imaging), the prognostic model will be estimated solely for the time period 2014–2017 and compared to the model estimated for the whole time period [1].

#### Exploratory analysis

Individual patient data from a prospective Italian cohort study is available to the research team [31]. The variables collected in the Italian study and how they compare to the variables being collected in our study are shown in Table 2. If most factors present in the multivariable model developed in our study are present in the Italian data set, then we will assess the effect of these factors on the risk of deterioration in a multivariable model derived in the Italian data set. If the effect estimates are similar to those estimated in the data collected in England, then we will combine the individual patient data of the two data sets to improve the precision of the model estimates.

**Table 2 Tab2:** Comparison between Italian data set and data being collected

Factor	In Italian data	Factor	In Italian data
Age	Yes	Equal pupils 1st examination	Yes
Sex	Yes	Both pupils reactive 1st examination	Yes
Pre-injury anti-coagulant use	Yes	SIGN of skull fracture 1st examination	No
Pre-injury anti-platelet use	No	Seizures in ED	No
Charlson Trauma Modified Comorbidity Index	Yes	Vomiting in ED	No
A pedestrian or cyclist struck by a motor vehicle	Yes	HAIS	No
An occupant ejected from a motor vehicle	Yes	Marshall Classification	Yes
A fall from height of > 1 m or 5 stairs	Yes	Single injury and type of injury	Yes
Mechanism of injury	No	Comment on midline shift	No
Amnesia	Yes	Comment on size of bleed	No
Loss of consciousness	Yes	Frailty score	No
Intoxicated time of injury	No	Admission Hb	No
Seizures before arrival ED	Yes	Admission platelets	No
Vomiting before arrival ED	Yes	Admission BM	No
GCS on arrival to ED	Yes	Additional injuries	Yes
BP on arrival ED	No		

## Discussion

### Strengths

To the authors’ knowledge, this will be the largest cohort study conducted that assesses clinical deterioration in GCS13–15 patients with brain injuries identified by CT imaging. We are collecting data from multiple sites and potentially incorporating data from a different European country. The definition of clinical deterioration is wide and defined to encompass potential benefits of hospital admission from the ED. This outcome is one that can be used to help inform clinical decision making regarding the selection of patients in this group that would benefit from hospital admission.

### Limitations

Data collection is retrospective and will be limited by the nature and accuracy of the data clinically recorded. However, such data are likely to be applicable and implementable in current routine practice. Given the large sample size required for this study and the challenges of prospectively recruiting patients in the ED, a retrospective method for data collection represents a feasible and pragmatic data collection strategy.

Outcomes will only be assessed during hospital admission and re-attendances to the hospitals where data collection is occuring. This may underestimate deterioration following discharge especially if patients die in the community or deteriorate and are readmitted to a different hospital. We will estimate the effect of this possible bias by conducting a sensitivity analysis using data for the subset of patients registered on the Trauma and Audit Network Database where complete data following discharge is available.

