### Study outcome

The outcome of interest is a composite measure of clinical deterioration such that inpatient hospital admission was warranted; this includes death due to TBI or neurosurgery within 30 days of attendance, ICU intervention whilst an inpatient, seizure activity whilst an inpatient, drop in GCS by 2 or more points whilst an inpatient or a readmission to hospital within 30 days of injury related to TBI.

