#### Data extraction

The full case records of patients identified through screening as potentially meeting the inclusion criteria will be retrieved (Fig. 2). In patients who are confirmed to meet the inclusion criteria, all a priori candidate prognostic factors will be extracted from the case records. Demographic information will be extracted from data recorded at the time of presentation to the ED following head injury. Comorbidities, frailty and pre-injury medication use will be extracted from that recorded in the ED attendance and subsequent inpatient hospital admission documentation. Comorbidities recorded in the inpatient notes up to 1 year prior to the presentation following head trauma will be included in accordance with the method of data collection in a recent update of the Charlson Comorbidity Index [19].

The full inpatient records will be interrogated for evidence of intervention or clinical deterioration that would meet the composite outcome measure. Recorded patient ED and hospital admissions after discharge following the relevant admission for traumatic brain injury will be assessed for evidence of deterioration, intervention or readmission in the 30 days following the initial ED attendance.

Patients who were included in the national Trauma Audit and Research network (TARN) registry will be identified locally. Using an anonymous TARN study number, we will assess for any deaths recorded on the TARN registry within 30 days of admission.

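### As written, the TARN sensitivity analysis can estimate missed deaths in registered patients but not readmission or neurosurgery at another hospital, so it covers only part of the post-discharge bias it is meant to estimate

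*Protocol article*

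**What the plan says.** The composite outcome has three components that can arise after the patient has left hospital. Under Study outcome these are "death due to TBI or neurosurgery within 30 days of attendance" and "a readmission to hospital within 30 days of injury related to TBI".

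Limitations states where outcomes are looked for: "Outcomes will only be assessed during hospital admission and re-attendances to the hospitals where data collection is occuring". It then gives the consequence: "This may underestimate deterioration following discharge especially if patients die in the community or deteriorate and are readmitted to a different hospital". The remedy offered is a "sensitivity analysis using data for the subset of patients registered on the Trauma and Audit Network Database where complete data following discharge is available".

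Data extraction describes what the registry supplies. "Patients who were included in the national Trauma Audit and Research network (TARN) registry will be identified locally", and then, through an anonymous study number, "we will assess for any deaths recorded on the TARN registry within 30 days of admission". No other TARN outcome is named anywhere in the article. The share of the cohort that is registered is not given.

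**The concern.** The sensitivity analysis is the plan's only stated safeguard against missed post-discharge events, and it rests on the registered subset having complete follow-up. The extraction plan does not deliver that completeness for non-fatal events. A registered patient who is readmitted or has neurosurgery at another hospital is, on the text, as invisible as an unregistered one.

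This matters because the model is meant to identify patients who could be discharged from the ED, and Model accuracy refers to a 1/100 risk of deterioration after discharge. Few events are expected in the group the model calls low risk, so a small number of missed ones could change the conclusion about that group. A check that finds few extra deaths, if reported as an estimate of the whole bias from complete data, would reassure more than it should.

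Two smaller ambiguities follow. The registry search is for any death, while the outcome counts death due to TBI. And it is unclear whether TARN deaths feed the main outcome: their place under Data extraction suggests that they do, while the Limitations statement that outcomes are assessed only at the study hospitals suggests that they do not.

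**Working it through.** **Side-by-side reading.** For each outcome component that can occur after discharge, and each place it can occur:

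| Event after discharge | Seen at study hospitals | Seen through TARN (registered patients) |
|---|---|---|
| Death in the community | No | Yes, within 30 days; cause still to be attributed |
| Neurosurgery at another hospital | No | Not in the stated extraction |
| TBI-related readmission to another hospital | No | Not in the stated extraction |

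The first of the two routes named in Limitations is addressed, within the registered subset. The second is not.

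**The plan's own figures.** These reproduce and are not in dispute.
- Events needed for 99% sensitivity with a 1.4-point margin: 1.96² × 0.99 × 0.01 / 0.014² = 194. At 10% prevalence, N = 194 / 0.10 = 1940, against the stated figure of about 2000.
- Margin with 200 events: 1.96 × √(0.99 × 0.01 / 200) = 1.38 points (stated 1.4).
- Prevalence margin: 1.96 × √(0.1 × 0.9 / 2000) = 1.31 points (stated 1.3).

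**Fragility of the low-risk group.** Inputs from Sample size: N = 2000, prevalence 10%, sensitivity 99%. Specificity (Sp) is not stated, so 20%, 30% and 50% are assumptions. Every undetected event is assumed to lie in the low-risk group, which is a worst case.

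Low-risk n = 2000 × (0.10 × 0.01 + 0.90 × Sp). Observed events in it = 200 × 0.01 = 2. Undetected events are already in the group, counted as non-events, so n does not change.

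| Assumed Sp | Low-risk n | Observed risk | 1% of n | Total events needed to exceed 1/100 | Undetected events needed |
|---|---|---|---|---|---|
| 20% | 2 + 360 = 362 | 2/362 = 0.55% | 3.62 | 4 | 2 |
| 30% | 2 + 540 = 542 | 2/542 = 0.37% | 5.42 | 6 | 4 |
| 50% | 2 + 900 = 902 | 2/902 = 0.22% | 9.02 | 10 | 8 |

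As shares of the cohort, 2/2000 = 0.1% and 8/2000 = 0.4%.

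**What a deaths-only check leaves behind.** The number of missed events, their fatal share and TARN coverage are not given, so all three are assumed. Take 200 observed events and 5, 10 or 20 missed ones, of which 25% are fatal, with full TARN coverage.
- Recovered: 1.25, 2.5 or 5. Still unseen: 3.75, 7.5 or 15.
- True prevalence: 205/2000 = 10.25%, 210/2000 = 10.5%, 220/2000 = 11.0%.
- If all unseen events are in model-low-risk patients, an apparent sensitivity of 99% is in truth 0.99 × 201.25/205 = 97.2%, 0.99 × 202.5/210 = 95.5%, or 0.99 × 205/220 = 92.25%.
- If all missed events are fatal, the check recovers every one and sensitivity stays at 99%.

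**The case against.** The strongest reply has four parts.

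- **The check does measure something.** Community death is one of the two named routes, and a 30-day registry death search addresses it in registered patients. This stands. A reader might infer that the analysis cannot measure the bias at all; the documents do not support that.
- **TARN may hold more than deaths.** Data extraction does not say that deaths are the only item used, and an article may leave registry fields to a fuller protocol. It is true that the article cannot show what the registry contains, so it would be wrong to infer that TARN has no other follow-up. But the article is specific in both places, and the two statements do not match: one names deaths, the other claims complete data. That is a conflict in the text, not an omitted detail.
- **The limitation is disclosed, and cause of death is already fixed.** The under-ascertainment is openly acknowledged. Searching for any death need not mean counting any death, since Study outcome fixes the cause as TBI. Both replies have force. What remains is that the disclosed bias is said to be estimated when only part of it would be, and that a death found only in the registry still needs a cause.
- **The numbers do not measure the bias.** This stands. The specificities are assumed, and placing every missed event in the low-risk group is a worst case. Nothing in the documents says how many events occur at other hospitals.

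A reader might also infer that switching to death from any cause would put registered and unregistered patients on the same footing. It would align cause attribution, but community deaths in unregistered patients would still be unseen.

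**Conclusion.** The point holds in limited form: the completeness claimed in Limitations is wrong as written. The planned TARN extraction supports an estimate of missed 30-day deaths in registered patients. It does not support an estimate of missed TBI-related readmission or neurosurgery at other hospitals, which are part of the composite and one of the two routes the plan itself names. Because only registered patients are covered, the result may not carry over to the whole cohort.

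The size of the resulting bias cannot be derived from the documents. The figures of 2, 4 and 8 undetected events show how little it would take to move the low-risk group past 1/100, under the plan's prevalence and sensitivity, the assumed specificities and the worst-case placement. They are not an expected bias. No sample-size or precision figure in the plan is affected.

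**What to change.** 1. Reconcile Data extraction with Limitations. Either name the TARN fields, or another existing source, that capture non-fatal events at other hospitals, or limit the sensitivity analysis claim to 30-day mortality in registered patients.
2. State whether TARN deaths enter the main outcome or only the sensitivity analysis, and how a death found only in the registry is classified against the outcome's TBI-related definition.
3. For non-fatal events, add a short bounding table. At the threshold finally chosen, report the size of the model-low-risk group, its observed events, and the number of undetected events that would take its risk above 1/100.

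The cost is one corrected sentence with the clarification in item 2, one extra tabulation from data already being collected, and a more modest claim about what the TARN subset can show.

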### Further research

Prognostic models tend to perform optimistically using the data from which they were derived, and therefore, their accuracy requires external validation in separate data sets [12]. There are different strategies for this and we will attempt to validate the model derived from this study in a sub-population of a European prospective cohort of TBI patients that is currently ongoing (CENTER-TBI), with data expected to be available in 2018 [32, 33]. Our validation study will be subject to a separate protocol. If the model appears sufficiently accurate at identifying low-risk TBI, that patients could be safely discharged, implementation will be tested prospectively in the context of the NHS.

## Abbreviations

AIS: Abbreviated Injury Severity
CT: Computed tomography
GCS: Glasgow Coma Scale
NICE: National Institute for Health and Clinical Excellence
ROC: Receiver operating characteristic
TARN: Trauma Audit and Research Network
TBI: Traumatic brain injury
